## Abstract

**Introduction:**

Colorectal adenoma (CRA), the main precursor of colorectal cancer (CRC), has a high recurrence rate (5-year cumulative: 48 - 68%) and a malignant transformation risk (0.2 - 0.5%). Traditional Chinese Medicine (TCM) provides a potential method to improve risk assessment and prevention. Based on TCM theories and the characteristics of colorectal adenoma, we hypothesize that an integrated system combining TCM syndromes, constitution types, and modern medical parameters can better predict adenoma recurrence and CRC occurrence.

**Methods and analysis:**

This is a multicenter prospective cohort study. A total of 15,000 patients with colonoscopy-confirmed colorectal adenomas will be recruited from 12 tertiary hospitals in China. At baseline, TCM characteristics (syndromes, constitution, tongue and pulse features), endoscopic findings, and biological samples (tongue coating, saliva, stool, blood, tissue) will be collected. The participants will be followed up for 5 years with risk-stratified standardized colonoscopy intervals. The primary outcomes are adenoma recurrence and CRC occurrence. The secondary outcomes include identifying risk factors and developing a predictive model. Multivariable logistic regression, Cox models, and mixed-effects models will be used for data analysis. A comprehensive biobank will be established to support future mechanistic studies.

**Ethics and dissemination:**

Ethical approval has been obtained from the Institutional Review Board of the Affiliated Hospital of Nanjing University of Chinese Medicine. Written informed consent will be obtained from all participants, who can withdraw at any time without prejudice.

**Clinical trial registration:**

https://clinicaltrials.gov/study/NCT06136026, identifier NCT06136026.

## Introduction

1

Colorectal adenoma (CRA), characterized by abnormal proliferation of colorectal mucosal epithelium, represents the most significant precancerous lesion for colorectal cancer (CRC) (1). Global data indicate that the 5-year cumulative recurrence rate after adenoma resection reaches 48%-68%, with approximately 0.2%-0.5% progressing to malignancy (2). In China, with the widespread adoption of endoscopic screening, the detection rate of CRA has been steadily increasing (3). Both domestic and international guidelines consider that the current optimal treatment for CRA is endoscopic resection, which can significantly reduce the incidence of CRC (1–4). Expert consensus on endoscopic diagnosis and treatment for colorectal cancer and precancerous lesions in China (2023, Guangzhou) states that for colorectal adenomatous polyps or polyps with a long diameter ≥5 mm, endoscopic resection is recommended, and the follow-up interval should be comprehensively determined based on factors such as pathological nature, lesion size, and number (1). The European Society of Gastrointestinal Endoscopy (ESGE) guidelines and the National Comprehensive Cancer Network (NCCN) guidelines, on the other hand, suggest that different endoscopic treatment methods can be selected according to the different types of polyps (3, 4). While risk factors for CRA have been studied, with pathological diagnosis as the gold standard and endoscopic resection as the primary intervention, large-scale cohort studies are still needed for further validation (4). TCM has shown promise in the diagnosis and prevention of adenoma recurrence, though more evidence is needed to support its clinical efficacy and mechanisms (5).

The theory of TCM constitution and syndrome differentiation provides a unique theoretical framework for assessing overall health status. Research has demonstrated that in CRA, dampness-heat syndrome is associated with increased disease progression risk, while spleen deficiency syndrome correlates with poor postoperative recovery (6). Guidelines have identified phlegm-dampness, dampness-heat, and blood stasis constitutions as high-risk factors for adenoma development (7). Tongue and pulse diagnosis, as essential components of TCM diagnostics, offer non-invasive, convenient, and reproducible assessment methods. Studies have shown that tongue features correlate with adenoma pathology: pale tongue with tubular adenomas, purple tongue with villous adenomas, and thick white coating with tubular-villous adenomas (7).

In addition, the potential of biological sample analysis in CRA screening and prognostic evaluation has drawn increasing attention. Studies have demonstrated that the tongue-coating lipidome in CRA patients shows significant differences compared to both healthy individuals and CRC patients, with nine key lipid species (AUC = 0.9) enabling effective discrimination between CRA and CRC (8). Specific lipids may serve as biomarkers for distinguishing adenomas and identifying malignant transformation. Analyses of saliva and fecal microbiota in patients with colorectal polyps also reveal statistically significant differences in structure and diversity compared to healthy controls (9). Shifts in the relative abundance of certain genera have been validated as diagnostic biomarkers for polyps, either individually or in combination. While conventional markers such as serum CEA and CA19–9 are associated with colorectal tumor progression, they often suffer from limited specificity and high testing costs. Recently, omics-based biomarker research has paved new avenues for the prognostic evaluation of adenomas.

Current research faces three main limitations: first, the lack of standardized assessment systems for constitution classification, syndrome diagnosis, tongue/pulse feature evaluation, and biological sample collection affects result comparability and reproducibility; second, small sample sizes limit statistical power; and third, short follow-up periods preclude long-term prognosis evaluation. While some studies suggest associations between specific TCM constitutions, syndromes, and biomarkers with adenoma recurrence risk, the evidence level remains low, necessitating more rigorous prospective studies.

Based on these considerations, we have designed this multicenter, prospective cohort study to enroll 15,000 CRA patients for a 5-year follow-up, systematically evaluating the associations between TCM constitution, syndromes, tongue/pulse features, multi-omics biomarkers, and adenoma recurrence and malignant transformation risk. This cohort systematically collected the exposure of patients to risk factors related to CRA, such as dietary structure, history of smoking and alcohol consumption, family history of polyps, etc., and followed up the pathological conditions of polyps in the same patients, aiming to explore the relationship between the occurrence and carcinogenesis of CRA and related risk factors.The primary objectives are to: (1) establish a standardized integrated TCM-Western medicine adenoma case and sample database; (2) assess correlations between various exposure factors and adenoma recurrence/progression; and (3) develop an integrated prognostic prediction model incorporating TCM and Western medicine characteristics (10). The characteristics of this cohort are: (1) wide distribution of centers across various regions in China; (2) significant differences in diet and climate across regions, enabling exploration of regional variations in adenomas; (3) comprehensive collection of information including patients’ demographic data, adenoma-related risk factors, medical history, TCM symptoms and constitution, examination results, etc.; (4) instead of solely collecting patients with a specific TCM syndrome type, focusing on specific symptoms and TCM constitution of patients, allowing for interpretation of rich syndrome types. This study’s innovations include: conducting the first large-scale multidimensional prediction study, implementing standardized assessment protocols, and integrating traditional TCM diagnostics with modern biomarkers. The results will provide crucial evidence for developing precise risk assessment systems and individualized prevention strategies.

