#### Sample size

2.3.6

For this multicenter prospective cohort study, we calculated the sample size based on two primary outcomes: CRA recurrence and CRC occurrence. According to previous studies, the detection rate of CRA ranges from 15%-30% during 3-year follow-up and reaches 48%-68% during 5-year follow-up, while the annual incidence of CRC among adenoma patients is approximately 0.2%-0.5%.

We employed the cohort study sample size calculation formula N = (Zα/2 + Zβ)² × P(1-P)/d², where Zα/2 = 1.96 (α = 0.05, two-sided), Zβ = 1.28 (statistical power = 90%), and d represents the acceptable margin of error. Two primary outcomes guided our sample size determination: CRA recurrence and malignant transformation.

For the adenoma recurrence outcome, we considered the 5-year cumulative recurrence rate ranging from 48% to 68%, with a median of 58%. Using an absolute error of 2%, the minimum sample size calculation yielded 6,394 cases. After accounting for a 20% potential loss to follow-up, the adjusted sample size was 7,993 cases.

Regarding malignant transformation, the occurrence rate was estimated between 0.2% and 0.5%, with a median of 0.35%. We applied a relative error of 50% (0.175%), which resulted in a minimum sample size of 11,970 cases. Incorporating the 20% follow-up loss adjustment, the final target became 14,963 cases.

Considering the statistical requirements, research resources, and the need for robust analysis, we ultimately set the total enrollment target at 15,000 participants. This approach ensures adequate statistical power to detect clinically meaningful differences while providing comprehensive insights into CRA progression and cancer risk. This sample size ensures adequate statistical power to detect clinically meaningful differences in both primary outcomes while accounting for potential loss to follow-up. An interim analysis will be conducted when 50% of the target sample size is achieved.

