## Strengths and limitations of this study

➢ This is the first large-scale multicenter study integrating TCM and Western Medicine for CRA risk prediction.➢ The research employs a comprehensive cohort of 15,000 patients with multimodal biological sampling and 5-year prospective follow-up.➢ Advanced statistical modeling and machine learning techniques provide innovative approach to risk stratification.➢ The single-country study design may limit global generalizability of findings.

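### On the planning figures about 42 cancers are expected, too few for a broad integrated prediction model for CRC; recurrence is unaffected

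*Protocol article*

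**What the plan says.** The third primary objective in the Introduction is to "develop an integrated prognostic prediction model incorporating TCM and Western medicine characteristics"; the Abstract lists a predictive model among the secondary outcomes. The Abstract's hypothesis is that a system combining syndromes, constitution types and modern medical parameters "can better predict adenoma recurrence and CRC occurrence". Section 2.3.2 ties the multi-omics work to malignant transformation as well as recurrence. A multidimensional model for CRC is therefore a declared aim.

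On methods, the Abstract states: "Multivariable logistic regression, Cox models, and mixed-effects models will be used for data analysis". Section 2.3.10 adds competing-risk and time-dependent Cox models. The strengths and limitations list adds, without naming a technique: "Advanced statistical modeling and machine learning techniques provide innovative approach to risk stratification".

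On the CRC rate, section 2.3.6 gives two descriptions of one range. Its opening paragraph says "the annual incidence of CRC among adenoma patients is approximately 0.2%-0.5"%. Its calculation says "the occurrence rate was estimated between 0.2% and 0.5%, with a median of 0.35"% and uses that figure as a single proportion. The Introduction has "with approximately 0.2%-0.5% progressing to malignancy", next to the 5-year recurrence figure.

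**The concern.** The number of outcome events, not the number of participants, limits how complex a prediction model can be. The cohort is large, but CRC is rare. Section 2.3.6 sizes the study for the precision of one proportion per outcome, which says nothing about how many predictors 42 cancers can carry. A rich model fitted to so few events tends to show good discrimination in the data that built it, poor discrimination in new patients, and predicted risks that are too extreme. The article intends its results to feed risk assessment, individualised prevention and follow-up strategy, so a CRC model of that kind could mislead.

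**Working it through.** **1. Reproduce the plan's figures.** Section 2.3.6 uses N = (Zα/2 + Zβ)² × P(1−P)/d², with "Zα/2 = 1.96 (α = 0.05, two-sided), Zβ = 1.28 (statistical power = 90"%).
- Recurrence, P = 0.58, d = 0.02: 3.24² × 0.58 × 0.42 / 0.02² = 6,393 (stated 6,394).
- CRC, P = 0.0035, d = 0.00175: 3.24² × 0.0035 × 0.9965 / 0.00175² = 11,955, or 11,966 with unrounded z values (stated 11,970).
- Loss of 20%: 11,970 / 0.8 = 14,962.5, stated as 14,963.

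The figures reproduce within rounding, so 0.35% was used as a plain proportion over the whole study.

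**2. Expected events**, with 15,000 × 0.8 = 12,000 evaluable.

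| Outcome and reading | Formula | Events | Range over 0.2% to 0.5% |
|---|---|---|---|
| CRC, plain proportion | 12,000 × 0.0035 | 42 | 24 to 60 |
| CRC, annual over 5 years | 12,000 × (1 − 0.9965⁵) | about 209 | 120 to 297 |
| Recurrence | 12,000 × 0.58 | 6,960 | – |

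**3. Size of the candidate pool.** Section 2.3.2 lists variables collected, not model terms. A plain count gives 11 demographic, lifestyle and history items, 4 endoscopic features, 4 pathology parameters (adenoma type takes two), 5 routine laboratory items, 4 markers and 9 symptoms: 11 + 4 + 4 + 5 + 4 + 9 = 37. This is before any syndrome, constitution, tongue, pulse or omics term. Models of 20 and 34 predictors are used below as illustrations. With 34, events per parameter are 42/34 = 1.2, or 209/34 = 6.1 on the annual reading.

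**4. Noise check.** Unpenalised logistic regression was simulated with n = 12,000 and predictors unrelated to outcome.

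| Events | Predictors | Apparent AUC | AUC in new data |
|---|---|---|---|
| 42 | 34 | 0.74 | 0.50 |
| 42 | 20 | about 0.68 | 0.50 by construction |
| 209 | 34 | 0.61 | 0.50 |
| 6,960 | 34 | 0.53 | 0.50 |

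**5. Check with real signal**, true AUC 0.70 and 34 predictors.

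| Events | Apparent AUC | New-data AUC | Calibration slope |
|---|---|---|---|
| 42 | 0.80 | 0.63 | 0.38 |
| 209 | 0.72 | 0.68 | 0.76 |

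**6. Supportable parameters.** For an expected shrinkage of 0.9, the maximum number is n × (0.9 − 1) × ln(1 − R²CS/0.9), where R²CS is the assumed Nagelkerke R² times its maximum. The documents give no R². A range of 0.04 to 0.15 is assumed; 0.04 is roughly what a true AUC of 0.70 implies at this event rate.
- Plain proportion (risk 0.35%, maximum R²CS 0.0455): at 0.15, R²CS = 0.00683 and the limit is 9.1; at 0.04, R²CS = 0.00182 and the limit is 2.4.
- Annual reading (5-year risk 1.738%, maximum R²CS 0.1608): the limits are 32.6 and 8.6.
- Thirty-four parameters at a risk of 0.35% would need about 44,700 participants even at R² 0.15.

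**The case against.** The strongest reply is that the article never describes the model being criticised. A reader might infer that some 34 predictors will go into one unpenalised CRC regression, and that its discrimination will be an artefact. The documents do not support that. The objective names no predictor list and no fitting method. Section 2.3.10 presents its regressions mainly as analyses of risk factors and associations, and a penalised logistic or Cox model would still fit the Abstract's wording. Variable selection, penalisation and validation may sit in an analysis plan that is not shown, so their absence is not counted here. The tally of candidates is the review's own.

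The reply is also right about the rate. If 0.2% to 0.5% is annual, a 34-predictor noise model shows an AUC of only about 0.61, which would not look impressive, and up to about 33 parameters could be carried at the favourable end of the assumed R².

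What survives is the limit set by the event count. An analysis plan can choose the terms but cannot add cancers: even if all 15,000 were evaluable, the planning rate gives 15,000 × 0.0035 = 52.5. Selecting terms from a large pool by the data also uses up information, and an unspecified reference to machine learning is no remedy at this number of events. The calculations do not, however, establish one exact number of terms, nor a ban on omics variables.

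**Conclusion.** The point holds conditionally. With 0.35% as a plain proportion and 12,000 evaluable, about 42 cancers cannot support a broad multidimensional CRC model fitted with the standard regression families named. About 2 to 9 parameters are supportable, and 20 to 34 unpenalised terms would give an apparent AUC of about 0.68 to 0.74 from noise alone. On the annual reading the problem is moderate: about 9 to 33 parameters are supportable, and the calibration slope is about 0.76 with 34 predictors and a true AUC of 0.70. These sizes rest on the assumed Nagelkerke R² of 0.04 to 0.15, on 20% loss, and on model sizes chosen for illustration. The integrated model for recurrence is not in question.

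**What to change.** 1. In section 2.3.6, state whether 0.2% to 0.5% is annual or cumulative over five years, align the Introduction and the calculation with it, and give the expected number of cancers.
2. Keep the full integrated model for adenoma recurrence.
3. For CRC, prespecify a small set of terms within a parameter budget derived from that expected number, with the assumed R² stated. Any omics terms count against the budget.
4. Fit the CRC model by penalised likelihood, report optimism-corrected AUC and calibration slope, and label it exploratory.

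The cost is wording in the protocol and analysis plan; no further data are needed. The downside is that the claim about predicting CRC becomes narrower and exploratory.

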## Methods and analysis

2

### Trial design

2.1

This study is designed as a longitudinal, prospective, large-sample, multicenter cohort study with an integrative Chinese and Western medicine approach, focusing on patients with CRA in China. The study aims to systematically follow patients from the time of adenoma diagnosis through potential progression or recurrence stages, providing comprehensive data on the natural history, risk factors, and outcomes of CRA in the Chinese population. This integrative research model combines TCM perspectives with modern Western medical approaches to create a more comprehensive evaluation system.

### Study population

2.2

This study will recruit 15,000 newly diagnosed CRA patients across 12 hospitals in China. As a prospective, multicenter integrative Chinese-Western medicine cohort study, we will confirm CRA diagnosis through colonoscopy and pathological verification, adhering to the ‘Consensus on Pathological Diagnosis of Gastrointestinal Adenoma and Benign Epithelial Polyps’ (11) (Digestive System Group, Chinese Pathology Society). Participating medical centers encompass diverse geographic regions across eastern, central, and western China, with patient populations including referrals from external institutions to ensure broad demographic representation. Tertiary hospitals with specialized facilities were selected as research centers, possessing substantial expertise in standardized colonoscopic procedures and pathological diagnosis to guarantee diagnostic accuracy and follow-up integrity.

Inclusion criteria: (1) meeting the diagnostic criteria for CRA; (2) age ≥18 years; (3) signed informed consent.

Exclusion criteria: (1) history of malignant tumors; (2) previous radiotherapy, chemotherapy, or colorectal surgery; (3) severe cognitive impairment, dementia, or psychiatric disorders.

### Interventions

2.3

#### Study measures and collection procedures

2.3.1

This prospective, multicenter cohort study of CRA in China will implement a comprehensive data collection protocol to ensure high-quality research data. All measurements will be conducted according to standardized procedures across all participating centers (**Figure 1**).

**Figure 1 f1:**
[figure not shown]
Comprehensive technical roadmap for colorectal adenoma surveillance and outcome analysis.

#### Baseline and follow-up data collection

2.3.2

At baseline, demographic information including age, gender, height, weight, smoking status, alcohol consumption, dietary habits, physical activity patterns, family history, medical history, and concomitant medications will be collected through structured interviews by trained research staff. This information will provide valuable context for understanding risk factors associated with CRA development and recurrence (**Table 1**).

**Table 1 T1:** Data collection and measurement schedule.

Time Point		Baseline	Follow-up(T1)	Follow-up(T2)	Follow-up(T3)	Follow-up(T4)	Follow-up(T5)
		-7–0 days	12 months	24 months	36 months	48 months	60 months
Demographic data	Medical history	✓	✓	✓	✓	✓	✓
	Family history	✓	–	–	–	–	–
Clinical examination	Colonoscopy findings	✓	✓	✓	✓	✓	✓
	Pathological examination	✓	✓	✓	✓	✓	✓
Laboratory tests	Complete blood count	✓	–	–	–	–	–
	Blood biochemistry	✓	–	–	–	–	–
	Fecal occult blood test	✓	–	–	–	–	–
	Tumor markers	✓	–	–	–	–	–
TCM syndrome evaluation	TCM syndrome questionnaire	✓	✓	✓	✓	✓	✓
	Tongue diagnosis	✓	✓	✓	✓	✓	✓
	Pulse diagnosis	✓	✓	✓	✓	✓	✓
Biological samples	Blood	✓	–	–	–	–	–
	Tongue coating	✓	–	–	–	–	–
	Stool	✓	–	–	–	–	–
	Saliva	✓	–	–	–	–	–
	Adenoma tissue	✓	–	–	–	–	–
Risk factor assessment	Smoking and alcohol use	✓	✓	✓	✓	✓	✓
	Dietary habits	✓	✓	✓	✓	✓	✓
	Physical activity	✓	✓	✓	✓	✓	✓
Treatment information	Western medical treatment	✓	✓	✓	✓	✓	✓
	TCM treatment	✓	✓	✓	✓	✓	✓
	Concomitant medications	✓	✓	✓	✓	✓	✓
Outcome assessment	Adenoma recurrence	–	✓	✓	✓	✓	✓
	Colorectal cancer occurence	–	✓	✓	✓	✓	✓

Demographic data, family history, tongue coating, and saliva samples are collected only at baseline, while most clinical and laboratory measurements are repeated at each follow-up visit to track changes over time and identify potential predictors of adenoma recurrence or progression.

Baseline TCM diagnostic information (tongue appearance, pulse characteristics, and symptomatic manifestations) will be collected simultaneously by trained research personnel. Collection timing will be strictly standardized to 24–48 hours post-admission and prior to colonoscopy, exclusively during morning fasting state (8-hour food restriction, 2-hour fluid restriction) to eliminate temporary interference from dietary intake or endoscopic procedures. This observational study will enroll only patients with first-time CRA detection (confirmed through comprehensive history review and colonoscopy of no previous adenoma history). At baseline, participants will receive no adenoma-specific treatments (including oral Chinese herbal medicine, herbal enemas, or other TCM interventions). During hospitalization (mean duration ≤1 week), patients will receive only routine Western medications related to surgical procedures (e.g., bowel preparation agents), ensuring baseline TCM diagnostic data accurately reflected the pathological status. Post-discharge self-administration of Chinese herbal medications is possible; this aspect will be systematically monitored during the follow-up period.

Clinical data collection will focus on comprehensive documentation of adenoma characteristics through colonoscopy and pathological examination. Colonoscopy findings will include the number, size, location, and morphological features of adenomas. Pathological assessment will document adenoma type (tubular, tubulovillous, villous), degree of dysplasia, and margin status. These parameters are essential for risk stratification of patients and determination of appropriate surveillance intervals.

Laboratory examinations encompassed complete blood count, blood biochemistry (liver and kidney function, blood glucose), fecal occult blood test, and comprehensive biomarker profiling [traditional tumor markers (CEA, CA19-9), emerging biomarkers (neutrophil-to-lymphocyte ratio (NLR), triglyceride-glucose index (TyG) (12), and serum metabolites including glycerophospholipids/sphingolipids)] (13). Additionally, multi-omics data (genomics, transcriptomics, metabolomics) from CRA patients were analyzed to identify novel biomarkers associated with adenoma recurrence and malignant transformation. Baseline sampling was conducted within 7 days prior to initial endoscopic examination, while follow-up sampling was performed 48–72 hours before surveillance endoscopy, ensuring precise correlation between biomarker fluctuations and endoscopically confirmed adenoma status.

An important feature of this integrative Chinese-Western medicine research is the collection of TCM syndrome data. This will include:

TCM syndrome questionnaires focusing on major symptoms (abnormal stool characteristics, altered bowel habits, abdominal pain, abdominal distension) and minor symptoms (gastric discomfort, fatigue, fever, chills, headache).The TCM Constitution Questionnaire was developed by [name] from Beijing University of Chinese Medicine.Tongue diagnosis using standardized tongue imaging equipment developed by Zhejiang Cancer Hospital (**Figure 2A**). Equipped with a 60-megapixel Leica lens and D65 standard light source, this device ensures accurate tongue color reproduction. Participants were required to fast and abstain from water for 4 hours before data collection to avoid interference with tongue coating color. During imaging, participants sat upright in a quiet environment, extended their tongues naturally, and remained relaxed to minimize tongue deformation. Images were captured only after confirming no obstruction of the tongue, with requirements to fully display both the tongue body and coating. RGB values were recorded, using RGB (255, 224, 189) as the reference standard. Subsequent image processing involved standardization of RGB and HSV channels to ensure color consistency, and a stable algorithm was applied to improve the accuracy of tongue diagnosis.Perform pulse diagnosis using the standardized pulse diagnostic device developed by Dajing Traditional Chinese Medicine (**Figure 2B**). This device is fitted with high-sensitivity pressure sensors, which accurately contact the “Cun”, “Guan”, and “Chi” pulse positions on the wrist for data acquisition. Prior to measurement, participants fasted and refrained from water for 4 hours, maintained physical relaxation, and ensured correct wrist positioning. After the examiner confirmed the pulse points, participants placed their forearms on the device. The instrument automatically collected pulse waveforms and key parameters to ensure data reproducibility. Pulse data were uploaded to an analysis system, where an intelligent algorithm generated pulse diagnosis results. Key pulse waveform parameters included pulse amplitude and cycle, with output results classifying pulse patterns such as “Chen” (deep), “Shuo” (rapid), “Xu” (deficient), “Shi” (excessive), and "Chi"(slow).Blood samples: 6-8ml of whole blood was collected using EDTA anticoagulant tubes, processed within 4 hours to separate plasma, and stored at -80 °C.Tongue coating samples: collected using sterile swabs from patients in a fasting state before tooth brushing.Stool samples: collected fecal swabs before patient endoscopic treatment.Saliva samples: 5ml or more, collected after patients abstain from food, water, and oral hygiene for 1 hour.Adenoma tissue: collected during endoscopic procedures, with paired normal mucosa when possible.

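### The baseline timing rules do not exclude collection after bowel preparation, so the claim that they ensure accurate TCM data does not follow

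*Protocol article*

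**What the plan says.** All of the timing rules are in section 2.3.2 of the protocol article (Baseline and follow-up data collection).

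- **TCM signs (tongue, pulse, symptoms).** "Collection timing will be strictly standardized to 24–48 hours post-admission and prior to colonoscopy", and "exclusively during morning fasting state (8-hour food restriction, 2-hour fluid restriction) to eliminate temporary interference from dietary intake or endoscopic procedures".
- **Medication in the same admission.** No adenoma-specific or TCM treatment is given. Otherwise "patients will receive only routine Western medications related to surgical procedures (e.g., bowel preparation agents), ensuring baseline TCM diagnostic data accurately reflected the pathological status".
- **Questionnaire content.** The TCM syndrome questionnaire centres on "major symptoms (abnormal stool characteristics, altered bowel habits, abdominal pain, abdominal distension"), with further minor symptoms.
- **Stool swab.** The only specific rule is "collected fecal swabs before patient endoscopic treatment". The general rule for baseline sampling is within seven days before the initial endoscopy, and Table 1 gives a baseline window of -7 to 0 days.

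Section 2.3.10 (Statistical analysis) uses fecal 16S rRNA data, with α and β diversity, to validate the association between TCM syndromes and adenoma. The Discussion names the relation between TCM syndromes and prognosis as what the study explores.

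**The concern.** The article does not merely leave the order of assessment and bowel preparation open. It describes the timing as strictly standardised, gives the removal of temporary interference as its purpose, names bowel-preparation agents as permitted, and concludes that the baseline TCM data are therefore accurate. Yet these agents change stool form and bowel frequency, which are two of the four major questionnaire symptoms, and may plausibly affect the other two, pain and distension. A swab taken after purging may not represent the patient's usual flora.

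Two uses of the data are at stake. Baseline syndrome is a central exposure, so error in it weakens any association with recurrence or cancer. The 16S data are meant to give the syndromes biological support. If preparation status differs between patients or centres and shifts both the symptom answers and the swab, it could produce part of a syndrome–microbiome association by itself. The article does not ask for the time of preparation or its order relative to collection to be recorded, so the analysis might be unable to tell.

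**Working it through.** **Step 1: does any stated rule exclude a patient who has already taken bowel preparation?**

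| Rule | Where | Excludes collection after preparation? |
|---|---|---|
| 24–48 h after admission (TCM signs) | 2.3.2 | No; it is anchored to admission, not to preparation |
| Before colonoscopy (TCM signs) | 2.3.2 | No; preparation also precedes colonoscopy |
| Morning, 8 h without food, 2 h without fluid (TCM signs) | 2.3.2 | No; a purged patient can be fasting |
| 4 h without food and water (tongue imaging and pulse) | 2.3.2 | No; it separates capture from recent drinking, not from an earlier purge |
| Before endoscopic treatment (stool swab) | 2.3.2 | No |
| Within 7 days before the initial endoscopy (baseline samples) | 2.3.2, Table 1 | No; the window runs up to day 0 |

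An assessment on the morning of the procedure, after preparation, can therefore satisfy every rule for TCM signs at once. A swab taken after preparation and before endoscopic treatment satisfies every rule for stool.

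**Step 2: does the plan protect against comparable interference elsewhere?** It does. Under section 2.3.3, TCM data collection is suspended at follow-up in patients who report TCM use, and they are reassessed later, to separate treatment-induced change from genuine signs. The 4-hour fast is there to protect tongue-coating colour. Bowel preparation has no equivalent safeguard.

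**Step 3: how large could the effect be?** The plan gives no figure to reproduce, so this is an illustration.

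Inputs:
- Prevalence of dampness-heat: 28.7% (section 2.3.10).
- Assumed true 5-year recurrence: 66% with the syndrome and 55% without, a difference of 11 points. These average 0.287 × 66 + 0.713 × 55 = 58.2%, close to the 58% used in section 2.3.6.
- Assumed sensitivity and specificity of syndrome classification after preparation: 0.90 each, unrelated to outcome. Classification before preparation is taken as perfect.

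If all patients are affected:
- Classified exposed: 0.287 × 0.90 + 0.713 × 0.10 = 0.2583 + 0.0713 = 0.3296. Risk = (0.2583 × 0.66 + 0.0713 × 0.55) / 0.3296 = 63.6%.
- Classified unexposed: 0.0287 + 0.6417 = 0.6704. Risk = (0.0287 × 0.66 + 0.6417 × 0.55) / 0.6704 = 55.5%.
- Observed difference: about 8.1 of 11 points (74%). The risk ratio falls from 1.20 to 1.15.

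If 30% are affected, sensitivity and specificity average 0.3 × 0.90 + 0.7 × 1 = 0.97:
- Classified exposed: 0.2784 + 0.0214 = 0.2998, of whom 92.9% truly have the syndrome.
- Classified unexposed: 0.0086 + 0.6916 = 0.7002, of whom 1.2% truly have it.
- Observed difference: 11 × (0.929 − 0.012) = about 10.1 points, a loss of about 8%.

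If none are affected, nothing is lost.

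**The case against.** **The sentence may mean something narrower.** The assurance follows a statement that no adenoma-specific or TCM treatment is given, and may mean only that no such treatment distorts the signs. That is a fair reading of the intent. But the sentence names bowel preparation as the treatment that patients do receive, and nothing in the section shows that it leaves the signs unaffected.

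**Sequence may be left to operating procedures.** Section 2.3.9 promises SOPs for each aspect of data collection, and section 2.3.4 provides training and checks on sample collection. An SOP could well set the order. The point here is not missing detail, however: a rule presented as sufficient can be fully met with data collected after preparation.

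**The mechanism is not documented.** Symptoms are taken by interview (section 2.3.8.2), and a careful interviewer may record habitual bowel function. This stands in part: misclassification is possible, not established. Since the article gives no recall period, it cannot be ruled out either. Effects on tongue and pulse are inference only, and the point does not depend on them.

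**Consequences are limited.** The 16S work is supportive and is not a primary outcome, and syndrome is one of several exposures. If all patients had the same preparation status, it could not by itself create a syndrome–microbiome association. Both points stand.

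**A reader might infer a mismatch between baseline and follow-up samples**, because "follow-up sampling was performed 48–72 hours before surveillance endoscopy" whereas baseline has no minimum gap. The document does not support this. Table 1 schedules stool, saliva and tongue coating at baseline only, and the 48–72 hour rule concerns biomarker sampling, not TCM assessment.

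**Conclusion.** The point holds as a gap between a stated rule and the assurance drawn from it. Neither the rule for TCM signs nor the rule for the stool swab excludes collection after bowel preparation, so the accuracy of the baseline TCM data is not ensured.

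A reader might go further and conclude that the baseline data will be taken after purging, or that a quarter of any syndrome effect will be lost. The article supports neither. It permits such collection without showing that it occurs, and the share could lie anywhere from 0 to 100%. The loss of 0 to about 3 of 11 points is an assumed range resting on invented recurrence risks and classification error that is unrelated to outcome. Distortion of the syndrome–microbiome comparison further requires preparation status to vary between patients or centres, on which the article is silent.

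The change is still worth making: it is cheap, and Table 1 schedules no repeat of the baseline swab in a planned 15,000 patients.

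**What to change.** These changes concern the order and recording of measurements only, not the choice, dose or timing of bowel preparation.

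1. In section 2.3.2, require the baseline TCM questionnaire, tongue and pulse capture and stool swab to be completed before the first dose of any bowel-preparation agent. For consistency, do the same for the baseline saliva and tongue-coating samples.
2. Apply the same order to the TCM assessments repeated at follow-up (section 2.3.3). No follow-up stool, saliva or tongue-coating samples need to be added, since Table 1 schedules none.
3. Record the collection time and the time of the first preparation dose in the eCRF.
4. Flag data collected after preparation, and exclude them from the syndrome and microbiome analyses in a sensitivity analysis.
5. Delete the statement that receiving only procedure-related medication ensures accurate baseline TCM data.

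The cost is revised protocol and SOP wording and two time fields. The downside is that some patients must be assessed earlier in the admission or have their data flagged.
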